#### Process evaluation

Data on process evaluation will be analyzed, using qualitative and quantitative methods. Data from the qualitative interviews will be used to explore and distill relevant themes regarding treatment experiences among patients during the trial.

In principle, we aim to record 10% of administered sessions with audio devices in order to assess whether treatment sessions have been implemented according to protocol. Furthermore, quantitative data from items on the session rating scales (SRS) will be analyzed, using descriptive statistics in SPSS. For example, descriptive statistics per SRS item in both treatment arms may include: medians, means and frequencies. Using t-test analysis, differences in SRS outcomes between both treatment arms will be examined quantitatively in order to determine whether GST is more feasible than CBT-E for patients.

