#### Control treatment: individual enhanced cognitive behavioral therapy for eating disorders (CBT-E)

In general, CBT-E is a transdiagnostic ED treatment, meaning that it is widely used for most diagnosed EDs in mental healthcare. In addition to that, it is also considered the current standard of care for most EDs. An entire CBT-E trajectory consists of 20–40 individual sessions, each of which will last 60 min at most. In the current protocol, the first 8 CBT-E sessions for a patient will take place before randomization (phase 1 CBT-E). After being randomized to the continued CBT-E arm, the remaining 12–32 individual sessions will take place.

From a theoretical perspective, CBT-E is based on a so-called transdiagnostic CBT model consisting of four phases. In phase one, patients formulate a personal goal, in which they learn to monitor and establish regular eating behaviors in order to address their eating disorder. In doing so, patients are offered psycho-education on factors that are maintaining their eating disorder. In phase two, consisting of one session, a more specific treatment plan is developed, based on an evaluation of the first phase. During phase three, the identified main mechanisms that are hypothesized to maintain the patient’s ED are addressed. These are (1) an excessive evaluation of body image, (2) dietary restraint, and (3) events, mood and eating. Subsequently, a relapse plan is developed in order to maintain the newly established eating behaviors when faced with these challenging mechanisms. Lastly, phase four aims to evaluate and sustain the total progress that has been achieved during the prior phases.

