Subsequent to randomization, participants will complete measures before continued CBT-E or the start of GST (T0), immediately after the confirmed end date of treatment (T1), and 6 months (T2) and 12 months (T3) following completion of treatment. In addition to measuring perceived ED schemas, data on quality of life and healthcare service use will also be gathered on these occasions. Data on process evaluations, as assessed by session rating scales and patient registration files, will be collected during each treatment session of phase 1 CBT-E, continued CBT-E, and GST. After treatment (T1), a representative sample of ED patients from both arms will be recruited to participate in a qualitative interview to gain deeper insights into their treatment experiences. Due to the nature of the interventions, blinding of therapists, interviewers, and patients is not possible. Below, all measures are stratified for clinical effectiveness, economic evaluation and process evaluation.

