#### Process evaluation

In order to measure the extent to which GST is a feasible alternative to CBT-E in clinical practice for patients and therapists, process evaluations will be conducted. More specifically, treatment fidelity (treatment quality), dose delivered (completeness), dose received (exposure and satisfaction), and reach (participation rate) will be assessed in both the GST arm and the continued CBT-E arm.

I.In order to assess dose received, i.e. treatment satisfaction and overall therapeutic alliance, patients will complete a session rating scale (SRS) during each treatment session. The SRS consists of 4 questions regarding key dimensions of effective therapeutic relationships [53].

II. To assess dose delivered and reach, therapists will complete patient registration files after each session. In these files, therapists can describe patient attendance and the extent to which treatment was delivered according to protocol, including potential deviations and additional therapies or medications. These files are expected to assess the true implementation characteristics of the treatment protocol in Dutch clinical practice.

III. Recording of therapy sessions will take place regularly in order to rate overall compliance to the treatment protocol, quality of treatment delivery and the number of patients that were able to participate (fidelity, dose delivered and reach).

IV.After the end of treatment, qualitative interviews will be conducted among certain patients from the GST arm and the continued CBT-E arm, which will take approximately 30 min. Using existing guidelines for qualitative data collection and analysis [54], these interviews are aimed at generating original findings regarding patient experiences that are not identifiable through quantitative approaches. Building upon the SRS, these interviews may identify profound data regarding treatment satisfaction and therapeutic alliance.

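### A between-arm t-test of SRS ratings is meant to settle comparative feasibility, although the SRS covers only satisfaction and alliance, within one of the protocol's four feasibility components

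*Protocol article*

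**What the plan says.** Two parts of the protocol article bear on this.

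- **Data collection, Process evaluation.** The aim is to measure how far GST is a feasible alternative to CBT-E for patients and therapists. For this, "treatment fidelity (treatment quality), dose delivered (completeness), dose received (exposure and satisfaction), and reach (participation rate) will be assessed" in both arms. Each instrument then gets its task. For the SRS: "In order to assess dose received, i.e. treatment satisfaction and overall therapeutic alliance, patients will complete a session rating scale (SRS) during each treatment session". On its content: "The SRS consists of 4 questions regarding key dimensions of effective therapeutic relationships". Other components have other sources: "To assess dose delivered and reach, therapists will complete patient registration files after each session". Session recordings serve fidelity, dose delivered and reach, and interviews add to the picture of satisfaction and alliance.
- **Data analysis, Process evaluation.** SRS items are described per arm, and a t-test follows in which "differences in SRS outcomes between both treatment arms will be examined quantitatively in order to determine whether GST is more feasible than CBT-E for patients".

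On timing, the general part of Data collection says that SRS and registration data "will be collected during each treatment session of phase 1 CBT-E, continued CBT-E, and GST". Every patient therefore has SRS ratings from before randomisation.

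On expectations, the Background suggests that GST may reduce dropout and calls dropout a major hurdle in CBT-E. The clinical-effectiveness hypothesis includes better treatment adherence with GST.

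**The concern.** The analysis section draws from the SRS a conclusion that the data-collection section does not equip it to give. Four questions about the therapeutic relationship can show whether patients who attended were satisfied and felt allied with the therapist. They cannot show whether patients kept coming, whether the sessions were delivered, or whether they were delivered as intended.

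The gap matters because attendance and dropout are where the protocol expects the arms to differ. A patient who stops attending gives no further ratings. As worded, a significant SRS difference would license the statement that one treatment is more feasible for patients even if that treatment lost more of them. Conversely, a real gain in retention under GST would leave no trace in the test.

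**Working it through.** The plan gives no figure for the SRS comparison. Its only power figure, 232 patients, concerns the primary outcome and is not in question here.

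**Step 1. Components against instruments (no assumption needed).**

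| Component | Source named under Data collection |
|---|---|
| Fidelity | session recordings |
| Dose delivered | registration files, recordings |
| Reach | registration files, recordings |
| Dose received | SRS; interviews on satisfaction and alliance |

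The SRS serves one row of four. Within that row the component is glossed as exposure and satisfaction, and the SRS measures satisfaction and alliance, not exposure. In the analysis section, the only between-arm test tied to a feasibility conclusion is the SRS t-test.

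**Step 2. What the test cannot see (illustration).** Inputs: dropout d of 20% in one arm and 54% in the other, the ends of the range that the Background cites for CBT-E trials. My assumption: patients who drop out attend a quarter of their planned sessions. Share of planned sessions attended = (1 − d) + 0.25d.

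- d = 0.20: 0.80 + 0.05 = 0.85
- d = 0.54: 0.46 + 0.135 = 0.595

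If ratings at attended sessions are alike in both arms, the expected SRS difference is zero, although one arm delivers 85% and the other about 60% of planned sessions.

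**Step 3. Pooled session ratings (illustration only).** Further assumptions: dropouts rate 1 SD lower than patients who stay, and all session ratings are pooled. The share of ratings from dropouts is s = 0.25d / (0.25d + 1 − d). The arm mean is too high by d − s, in SD.

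- d = 0.20: s = 0.05/0.85 = 0.059; excess 0.14
- d = 0.30: s = 0.075/0.775 = 0.097; excess 0.20
- d = 0.54: s = 0.135/0.595 = 0.227; excess 0.31

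These are single-arm values. The contrast is distorted only by their difference: 0 with equal dropout, 0.20 − 0.14 = 0.06 SD at 20% versus 30%, and 0.31 − 0.14 = 0.17 SD at 20% versus 54%. In the last case, with equal ratings among patients who stay, the per-patient means differ by 0.54 − 0.20 = 0.34 SD and the pooled means by 0.227 − 0.059 = 0.17 SD. Pooling halves the difference but does not reverse it. With one mean per patient the distortion is zero.

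**The case against.** The fair defence is that the sentence speaks of feasibility for patients, while the wider aim covers patients and therapists. All four components are assessed in both arms, and the same analysis section also covers recordings and interviews. The three process research questions under Objectives ask for no comparative feasibility verdict, and no trial decision hangs on this test. On that view one purpose clause is loosely worded.

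Much of this stands, and it sets the severity. It does not remove the point. Attendance and dropout are patient-side matters, so limiting the claim to patients does not make the SRS sufficient. The other data are collected, but the stated conclusion does not draw on them.

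A reader might go further and infer that the contrast is biased in known ways. The documents do not support that.

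- **A head start for CBT-E from the 8 run-in sessions.** Controls do continue the same therapy: "After being randomized to the continued CBT-E arm, the remaining 12–32 individual sessions will take place". But nothing says that the therapist or the alliance carries over. GST patients have 5 individual preparatory sessions during the wait for a group. All randomised patients are early non-responders, so staying with CBT-E could lower ratings as well as raise them. Neither size nor direction is given. Continuing versus switching is also the contrast that the trial sets out to study.
- **Contamination by phase 1 ratings.** A comparison of the two treatment arms naturally means GST and continued CBT-E. Phase 1 is named separately.
- **A demonstrated dropout bias of 0.14 to 0.31 SD.** Those are single-arm values. They rest on assumed inputs and on pooling that the plan does not state. One value per patient is the ordinary input to a t-test. The 20–54% comes from the literature on CBT-E trials, not from patients who have already completed a run-in.

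**Conclusion.** The point holds as a mismatch between the conclusion attached to the SRS t-test and the protocol's own account of feasibility. This follows from the text alone and needs no numerical assumption. The SRS measures satisfaction and alliance at attended sessions. It does not measure attendance or dropout, so an arm that loses more patients could still be declared more feasible.

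No bias in the SRS contrast is established. The run-in head start remains a possibility of unknown size and direction. The figure of about 0.17 SD between arms applies only to pooled session ratings, 20% versus 54% dropout, dropouts rating 1 SD lower and stopping after a quarter of their sessions.

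Severity is minor. The process evaluation is affected; the EDE-Q comparison is not.

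**What to change.** Amend the SRS sentence in the process-evaluation part of Data analysis, and carry the same wording into any analysis plan:

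1. Describe the test as a comparison of treatment satisfaction and therapeutic alliance between arms, not as the test of feasibility.
2. Use post-randomisation ratings only, with one summary value per patient, adjusted for that patient's phase 1 SRS mean. In practice the t-test becomes a linear model with arm and the phase 1 mean. The covariate precedes randomisation and is already planned for every patient. It allows for differences between patients in how they rated phase 1, but it would not remove a head start should one exist.
3. Base any statement that one treatment is more or less feasible on all four components: reach, dose delivered, fidelity and dose received. Dose received stays among them.
4. Report attendance and dropout by arm beside the SRS result, including the number of patients with no post-randomisation rating.

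The cost is a change of wording and a little more analysis. The SRS, registration files and recordings are already planned, so no new data are required.

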## Discussion

By illuminating the clinical effectiveness of GST for treating EDs, including the interconnections between ED severity and schemas, our study findings may expand the existing body of evidence on the clinical potential of GST for treating (atypical) AN and BN patients not showing a rapid response after the first phase (8 sessions) of CBT-E. Due to unsatisfactory CBT-E treatment rates and the absence of a clinically dominant alternative in current practice for a substantial group of patients [6, 10], we are morally obliged to aim at developing effective treatment alternatives for this group. Taking into account ED healthcare and societal costs [4], the current study protocol will also examine whether GST is a cost-effective and feasible alternative to CBT-E in a specific subgroup from a health economic perspective.

### Study strengths

To our knowledge, this is the first study protocol initiating a multicenter RCT trial in clinical practice to examine the clinical effectiveness, cost-effectiveness and feasibility of GST as an alternative to CBT-E for eating disorder on a global scale. The multicenter RCT research design, enabling collaborations between research and clinical practice and people with lived experience, may greatly facilitate the organizing process of the current trial and may expand the existing body of evidence on GST in real clinical settings. As a result, our study may generate relevant impact in Dutch mental healthcare beyond academia. Using a declaration of intent, all institutions have declared their willingness to participate in the current trial.

Second, an extensive data collection procedure has been developed, enabling broad analyses of clinical effectiveness and cost-effectiveness. In addition to that, all clinical measurement instruments used are highly validated. Primarily, the EDE-Q [37], YSQ-S3 [40, 41], SMI-ED [42], EDQOL [44] and EQ-5D-5 L [45] have been applied extensively in the field of psychotherapy research.

Third, the tested data handling system mentioned earlier is expected to greatly facilitate and automate patient recruitment, consent and data collection, which is tailored to each patient’s individual timeline during the trial. Using these tested and automated processes, data collection is expected to unfold in a standardized manner, which may reduce the risk of incomplete information, major deviations and related errors in the collection process. If necessary, this system can always be adapted, based on emerging observations during data collection.

Last, the TIC-P questionnaire was tailored to our population of interest through a careful expert review. In a similar vein, the layout and length of the TIC-P has varied over time in previous research [63]. Health services research on initiatives for measuring worker wellbeing has illustrated the importance of tailored questionnaires in order to highlight aspects that are relevant to participants [64]. In light of these previous findings, a tailored and shorter TIC-P version is expected to capture the most prevalent cost categories among ED patients, making it more suitable for routine outcome monitoring in the current project. This may reduce the risk of incomplete data resulting from ED patients failing to align with a questionnaire that is not fully relevant to them.

### Operational challenges

Although we are confident about the general applicability and resilience of the current study protocol, there are certain operational challenges that require our consideration.

First, ED patients are at risk of comorbid physical and mental health complications [65]. Even though severely vulnerable and ill-protected ED patients will be excluded during the screening phase, we cannot rule out the possibility of ED patients terminating their research participation due to health complications in a subsequent research phase. As a result, there is an inherent risk of incomplete data, which we aim to address by conducting all statistical analyses according to the intention-to-treat principles. Additionally, information leaflets are tailored to the research treatment phases that apply to participating patients, supporting their treatment adherence.

Second, participating ED treatment centers could face implementation challenges due to several barriers [66], including financial constraints and management challenges on the organizational level. In order to address these issues, regular communication strategies and facilitation of the implementation processes are key. In light of this objective, we aim to organize regular meetings and we will establish consistent communication lines, both online and on-site. Newsletters are prepared regularly in order to convey important updates and to optimize the overall sense of community among our participating partners.

Third, completion of all measurements may require substantial efforts from participants. Given the number of relevant questionnaires being administered, a full measurement may take up to two hours to complete. Although encouraging visuals will be implemented digitally to facilitate completion of each measurement over an extended time span with regular breaks, completing all measurements in time may still be challenging for participants. If possible, completion of measurements will be supported on-site at the institutions.

Fourth, it may be difficult to identify which components or sessions of GST are most (cost-)effective, in case overall (cost-)effectiveness of GST is shown. In reality, different factors contribute to treatment success that may be indirectly related to GST and CBT-E delivery, including therapeutic alliance. In spite of this particular limitation, the extensive data collection procedures, including a process evaluation and qualitative interviews, are expected to generate valuable and broad insights regarding the (cost-)effectiveness of GST.

Last, all participating therapists are qualified in the field of GST: they are experienced in leading a patient group and they have completed a basic GST course. However, not all participating therapists will be equally familiar with GST principles from the start. In order to ensure consistent treatment delivery among patients, an overarching supervision plan for all participating treatment centers is developed and tailored to their existing organizational structures. Being an authority in the field of ST for eating disorders [23], [name]’s e-learnings will be provided to all participating therapists. These educational courses will be the foundation for discussion points during the overarching supervision meetings.

### Implications for healthcare policy and clinical practice

In the current project, we aspire to pave the way towards clinically meaningful and affordable care trajectories in daily practice for (atypical) AN and BN patients not showing a rapid response after the first phase (8 sessions) of CBT-E. In light of this objective, we aim to inform clinical practice, Dutch healthcare policymakers and insurance companies about the extent to which GST provides solid clinical value for money, as an alternative to the existing CBT-E. Given the substantial ED disease burden for both individuals and society as a whole, future research initiatives examining the clinical effectiveness and cost-effectiveness of GST are highly warranted.

## Data Availability

No datasets were generated or analysed during the current study.

## Abbreviations

AN: Anorexia nervosa
BN: Bulimia nervosa
CBT-E: Cognitive behavioral therapy - enhanced
ED: Eating disorder
GST: Group schema therapy
ICER: Incremental cost-effectiveness ratio
ICUR: Incremental cost-utility ratio
ST: Schema therapy
WTP: Willingness to pay
